| Definition of the Study population Individual patient data will be extracted from the medical records of all patients registered at linked general practices contributing to the CPRD GOLD and Aurum in England.  Patients will be included if they meet the following criteria:   - Patients over the age of 40 years - Registered to a CPRD ‘up-to-standard’ practice - Records available after the study start date (01/01/1998) - Sufficient data to define the index date (see table below)   Patients will be excluded if they meet the following criteria:   - Previous prescription of the exposure variable (antihypertensive, statin or antiplatelet) - Blood pressure >180 mm Hg or total cholesterol >7.5 mmol/L (in patients with high blood pressure or cholesterol, treatment is indicated regardless of risk)   Study entry criteria – Patients will enter the cohort on the index date, defined as:   \| **Exposure** \| Antihypertensive therapy \| Statin therapy \| Antiplatelet therapy \| \| --- \| --- \| --- \| --- \| \| **Index date definition** \| 12 months after the first systolic blood pressure reading ≥130 mm Hg \| 12 months after the first coded or calculated CVD risk of ≥5% \| 3 months after first CVD event \|   Study exit criteria   - Last date at which the most recent linked data are available from the CPRD (study end date, July 2018) - Date of the most recent data upload from the practice to which a given patient is registered - Date at which a given patient transfers out of a registered CPRD practice - Date of death or specific outcome of interest |
| Selection of comparison group(s) or controls Aim 1: Not applicable – single cohort in CPRD GOLD.  Aim 2: Not applicable – single cohort in CPRD AURUM.  Aim 3 will use propensity score matching and instrumental variable analysis – see Methods section below. |

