| Plans for addressing missing data There is potential for missing data in this study, particularly with variables such as ethnicity which are recorded with varying degrees of accuracy in routine practice. Because this analysis is focused on treatment for prevention of cardiovascular disease, accurate selection of the sample population is important and therefore any patients with insufficient data available to define their blood pressure or cardiovascular risk status at baseline (index date) will be excluded. Where there is no record of blood pressure lowering, statin or antiplatelet treatment, it will be assumed the patients were not exposed to blood pressure lowering, statin or antiplatelet treatment.  Patient eligibility includes only using ‘acceptable patients’ in the analysis, and therefore there is no need to impute age and sex. Where there is no record of smoking history or alcohol consumption, patients will be assumed to be non-smokers and non-drinkers. Likewise, those with no record of co-morbidities will be assumed to have no history of these conditions. All other covariates (including BMI, ethnicity and IMD) used in the prognostic or casual inference modelling will be imputed using multiple imputation. BMI and will be treated as a continuous variable.  All analyses of treatment associations with outcomes will be conducted by intention-to-treat, and patients moving practice after the index date (and therefore being lost to follow-up) will be censored at the point at which they are no longer active in the database. |

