| List of Appendices Appendix 1. Code lists for the primary outcomes |
| Amendments **Amendment 1 – 19/05/2019 (approved)**  **We clarify that aims 1 and 2 (prognostic model derivation and validation) of the study should include the whole population independently of whether patients are new or old users of preventative treatment; the causal inference analyses will focus on new users only:**  *L. Definition of the study population*  Patients will be excluded if they meet the following criteria:  Previous prescription of the exposure variable (antihypertensive, statin or antiplatelet; for causal inference analyses only)  **Amendment 2 – 28/06/2021 (approved 05/07/2021)**  **We have made the following revisions aimed at simplifying the analysis plan in light of the very large sample size and computational time required to conduct each analysis:** *C. Technical Summary / E. Objectives, Specific Aims and Rationale* Aims:  3) Use causal inference methods (multivariable regression, propensity score adjustment/matching, instrumental variable analysis) to examine whether modification of treatment could have an important impact on the risk of adverse events.  *L. Definition of the study population*  Study entry criteria – Patients will enter the cohort on the index date, defined as:   \| **Exposure** \| Antihypertensive therapy \| Statin therapy \| Antiplatelet therapy \| \| --- \| --- \| --- \| --- \| \| **Index date definition** \| 12 months after the first systolic blood pressure reading ≥130 mm Hg \| 12 months after the first coded or calculated CVD risk of ≥5% (equivalent to age ≥50 years for men and ≥60 years for women) \| 3 months after first CVD event \|   *N. Exposures, Outcomes and Covariates*  Positive controls are outcomes know to be affected by treatment (e.g. cardiovascular disease, death)  For causal inference analyses (only), sensitivity analyses will explore outcomes defined more broadly using primary care codes as well. *O. Data/ Statistical Analysis* We no longer plan to conduct an internal validation of the prediction models. The following text from the protocol is therefore redundant:  Where feasible and appropriate, each model will be internally validated using the bootstrap method, to allow optimism-adjusted estimates of calibration and discrimination performance to be obtained. Adjustment for overfitting will be undertaken using a uniform shrinkage factor identified from bootstrapping, followed by re-estimation of the cumulative baseline sub-distribution hazard function (and thus baseline cumulative incidence function) to maintain overall calibration between observed and predicted risks. Given the large sample size, overfitting is likely to be small (see sample size calculation above). If bootstrapping is computationally infeasible due to the large sample size, then a smaller random sample of the population will be used or alternative internal validation methods employed such as cross validation.  *Aim 3 – causal inference analysis*  For most of the outcomes described in this proposal, the association and magnitude of effect with treatment is not well defined in randomised controlled trials. We will therefore undertake causal inference work to examine whether modification of treatment could have an important impact on the risk of adverse events using two causal inference methods: multivariable adjustment, propensity score adjustment/matching and instrumental variable analysis.  For the analysis using multivariable adjustment, Cox proportional hazards models will be used to compare adverse event rates in each experimental group. Estimates will be adjusted for pre-specified variables thought to confound the relationship between treatment and adverse events.  For the analysis using propensity scores, we will conduct separate analyses adjusting for propensity score and matching via propensity score.  *Subgroup and sensitivity analyses*  Where possible and appropriate, analyses of treatment associations will be examined in subgroups of the population. These will include age, sex, baseline blood pressure and cardiovascular risk, by drug type/dose/intensity and past medical history. Subgroup definitions will be agreed by expert opinion or taken from an accompanying systematic review of previous trials, examining the same topic. For computational reasons (whereby only one imputation model is required for all subgroup analyses of each outcome), these analyses will only be undertaken using propensity score adjustment. *P. Plan for addressing confounding* Two approaches will be taken to determine whether observed associations are potentially subject to residual confounding.^46^ Where all approaches provide similar results, we can be more confident that the findings are accurate and reliable. Further steps will be taken to examine the validity of treatment effect estimates using positive and negative controls: the impact of treatment on an outcome known to be affected by treatment (e.g. cardiovascular disease and death; positive controls)  **Amendment 3 – 25.11.2021**  **We have added exploratory analyses using supervised machine learning approaches to address missing data and deal with confounding by indication in the causal inference analyses.** O. Data/ Statistical Analysis ***Aim 3 – causal inference analysis***  For most of the outcomes described in this proposal, the association and magnitude of effect with treatment is not well defined in randomised controlled trials. We will therefore undertake causal inference work to examine whether modification of treatment could have an important impact on the risk of adverse events using two causal inference methods: propensity score matching and instrumental variable analysis.  For the propensity score analysis, eligible patients will be matched 1:1 at the index date using propensity scores, which indicate the likelihood a patient will be prescribed treatment on the basis of their known (pre-treatment) characteristics and other known information which might influence the decision to treat. Predictors of preventative drug prescription will be explored in a logistic regression model. Matched patients will be compared using the Cox proportional hazards models, but hazard ratios will only be adjusted by factors unbalanced at baseline which are not already included in the propensity score model. Time since cohort entry will be used as the underlying time function in each model.  For the instrumental variable analysis, GP’s previous antihypertensive prescribing preferences will be used as an instrument to predict the likelihood of actual treatment. Risk of adverse events will be estimated in patients attending a GP considered a high prescriber of preventative medication and compared to those attending a GP considered a low prescriber. If the results from the propensity score matching suffer from unmeasured confounding, they will differ from those of the instrumental analysis. If this is the case, these models will be refined with additional factors to achieve better adjustment and matching. Where all approaches provide similar results, we can be more confident that the findings are accurate and reliable.^46^  Generative Adversarial Networks (GAN) will also be used to impute missing counterfactual data (unobserved effects of untaken treatments) on an individual level. GAN models are a class of machine learning frameworks that involves the simultaneous training of a pair of deep neural networks in competition with each other. The idea is that the first network, the generator, generates synthetic data samples that are similar to the original samples, while the second network, the discriminator, evaluates the authenticity of the generated samples [1]. Data similarity and fidelity are usually evaluated using well-known metrics such as Maximum Mean Discrepancies [2] and Jensen-Shannon Divergence [3]. While GAN’s initial uses were for imaging applications, its generative capabilities make it naturally suitable for generating missing values that can be used to impute the original samples.  In this work, we build on the intuition that treatment effects estimation and causal inference are a missing data problem, where counterfactuals (unobserved effects of untaken treatments) are missing [4]. Specifically, we plan to use GAN to impute missing counterfactual data, for the samples available in CPRD. By modifying the generator’s goal to accurately impute missing data, and the discriminator’s goal to distinguish between observed and imputed counterfactual values for the same patient record. The model can generate the missing data conditional on the observed values and assigned treatment for each patient as seen in [5, 6]. While useful, the work of [5, 6] are not compatible for time-series data nor for estimating multiple treatment effects, which limits its use in real-life treatment applications. Therefore, we plan to extend such previous works to make them compatible for multiple treatment options and for time-series data to allow for long-term treatment (antihypertensives, statins, antiplatelets) estimation effects for multi-morbid populations as initially proposed in this project.  The proposed GAN approach does not generate new patient samples, but rather generates counterfactual (missing component) conditioned on observed factual data, and outputs a complete record with both factual and counterfactual outcomes to allow for treatment effect estimation for each patient. This approach is naturally immune to re-identification attacks since no new samples are generated, but we will run privacy checks and measures within the data to verify that the model is not copying potential outcomes from patients in the training sample. Example privacy measures that we plan to apply include empirical evaluations such as mathematical privacy definitions such as identifiability [7] that quantifies the probability of re-identification to ensure that no combination of attributes could reveal the identity of a patient. Other privacy evaluation methods include testing that the model is robust against membership inference attacks, where an attacker attempts to determine if a specific patient was used in the training set of the model [8]. Lastly, we will experiment with strict theoretical guarantees such as differential privacy which allow for the model to learn almost nothing about an individual while learning useful information about a population [9].  **References**  [1] Ian Goodfellow, Jean Pouget-Abadie, Mehdi Mirza, Bing Xu, David Warde-Farley, Sherjil Ozair, Aaron Courville, and Yoshua Bengio. Generative adversarial nets. *Advances in neural information processing systems*, 27:2672–2680, 2014.  [2] Arthur Gretton, Karsten M Borgwardt, Malte J Rasch, Bernhard Sch¨olkopf, and Alexander Smola. A kernel two-sample test. *The Journal of Machine Learning Research*, 13(1):723–773, 2012.  [3] AP Majtey, PW Lamberti, and DP Prato. Jensen-shannon divergence as a measure of distinguishability between mixed quantum states. *Physical Review A*, 72(5):052310, 2005.  [4] Peng Ding and Fan Li. Causal inference: A missing data perspective. *Statistical Science*, 33(2):214– 237, 2018.  [5] Jinsung Yoon, James Jordon, and Mihaela Schaar. Gain: Missing data imputation using generative adversarial nets. In *International Conference on Machine Learning*, pages 5689–5698. PMLR, 2018.  [6] Jinsung Yoon, James Jordon, and Mihaela van der Schaar. Ganite: Estimation of individualized treatment effects using generative adversarial nets. In *International Conference on Learning Representations*, 2018.  [7] Jinsung Yoon, Lydia N Drumright, and Mihaela Van Der Schaar. Anonymization through data synthesis using generative adversarial networks (ads-gan). *IEEE journal of biomedical and health informatics*, 24(8):2378–2388, 2020.  [8] Reza Shokri, Marco Stronati, Congzheng Song, and Vitaly Shmatikov. Membership inference attacks against machine learning models. In *2017 IEEE Symposium on Security and Privacy (SP)*, pages 3–18. IEEE, 2017.  [9] Cynthia Dwork, Aaron Roth, et al. The algorithmic foundations of differential privacy. *Found. Trends Theor. Comput. Sci.*, 9(3-4):211–407, 2014.  **Amendment 4 – 30.11.2022**  **Added University of Birmingham to the list of data processors.** |

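### Aim 3 is limited to new users, but no registered time is required before the qualifying date, so some continuing users can be counted as initiators

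*Protocol*

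**What the plan says.** Under Definition of the Study population, the protocol lists four inclusion criteria. One is age. The other three are "Registered to a CPRD ‘up-to-standard’ practice", "Records available after the study start date (01/01/1998" and "Sufficient data to define the index date (see table below". None of them sets a minimum time that the patient must have been registered before the date that qualifies them.

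The first exclusion reads "Previous prescription of the exposure variable (antihypertensive, statin or antiplatelet" and gives no period and no reference date. Amendment 1 confines this exclusion to Aim 3 and explains that "the causal inference analyses will focus on new users only".

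The index date is "12 months after the first systolic blood pressure reading ≥130 mm Hg" for antihypertensives and "12 months after the first coded or calculated CVD risk of ≥5" per cent for statins. For antiplatelets it is three months after a first cardiovascular event. Each interval runs forward from the qualifying date.

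Plans for addressing missing data adds two defaults. A patient without a treatment record counts as unexposed, and "those with no record of co-morbidities will be assumed to have no history of these conditions".

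**The concern.** Whether a patient is a new user can be judged only from time in which a prescription would have been seen. If a patient may qualify on the day of joining the practice, that time can be zero. A person already taking an antihypertensive who registers, has a qualifying systolic reading soon afterwards and then has the drug re-issued shows no earlier prescription in the record. That person enters the treated group as an initiator.

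Patients who continue a drug have, on the whole, tolerated it. Counting them as initiators depletes the treated group of those most susceptible to harm, which is the problem a new-user restriction exists to prevent. Aim 3 is the part of the study that estimates harm caused by treatment, and the wider programme intends to build a patient-facing calculator.

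The planned checks do not target this fault. The negative control outcomes look for confounding, not for depletion of susceptible patients. The instrumental variable analysis uses the same new-user restriction, so agreement between the methods could reflect a shared error.

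**Working it through.** **Reading the rules together**

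1. *Observed time before the qualifying date.* The eligibility list, the linked-data section, the analysis section, the missing-data section and the amendments supply no minimum. Up-to-standard status describes the practice, not how long the patient has been there.
2. *What previous must refer to.* The analysis section defines exposure for the Aim 1 models as a prescription in the year before the index date. The primary analyses assume that treatment does not change afterwards. If Aim 3 fixes exposure in the same way, an exclusion for prescriptions before the index date would remove the exposed group. Previous must then mean before the qualifying date, which is the period with no guaranteed observation.
3. *Who gets through.* Only patients whose first recorded prescription falls on or after the qualifying date. One recorded earlier still excludes them.
4. *Which cohorts.* The gap applies directly to antihypertensives and statins. Amendment 2 equates the 5% risk threshold with age 50 or over in men and 60 or over in women. If that is applied as an age rule, an older joiner can qualify on registration, and every re-issue follows the qualifying date. For antiplatelets, hospital data are to be used for eligibility, with earlier cardiovascular disease as the example. This partly guards against a false first event, but hospital data are not described as supplying prescriptions.

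**The plan's own figure**

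Inputs from Sample size considerations: hazard ratio 1.10, control rate 0.5% a year, 90% power, alpha 0.05 (taken as two-sided), 1:1 groups.

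- Events (Freedman) = (1.960 + 1.2816)² × (2.1 / 0.1)² = 10.507 × 441 = 4,634, as stated.
- Control risk over 10 years = 10 × 0.005 = 0.05. The 10-year horizon is inferred because it reproduces the result. Treated risk = 1 − 0.95^1.1 = 0.05486, and the mean is 0.05243.
- Patients = 4,633.8 / 0.05243 = 88,380, as stated.

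**Illustration of dilution**

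The documents give no share of continuing users, so both the share m and their hazard ratio h are assumptions. With a simple mix, the apparent ratio is (1 − m) × 1.10 + m × h.

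| m | h = 1.0 | h = 0.9 |
|---|---|---|
| 5% | 1.095 | 1.09 |
| 10% | 1.09 | 1.08 |
| 20% | 1.08 | 1.06 |
| 30% | 1.07 | 1.04 |

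This table covers only the tolerance mechanism.

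**Why power is not the issue**

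At exactly 4,634 events, an apparent ratio of 1.07 would give about 63% power. But 4,634 is the required minimum, and Feasibility counts expects 216,000 falls and 230,000 myopathy or muscle pain events. If only a tenth of the falls (21,600) entered a 1:1 comparison, z = √21,600 × 0.07 / 2.07 = 4.97. That exceeds 1.96 by 3.01, so power is above 99%.

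**The case against.** Several points on the other side stand.

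- *Not every joiner passes.* A reader might infer that anyone who arrives already on treatment becomes a new user. The exclusion has no time limit, so a repeat issued before the qualifying date removes the patient.
- *Power.* A reader might infer a fall from 90% to about 63%. That holds only at the minimum event count, far below what is expected for falls and muscle outcomes. The 1,200 intracranial haemorrhages expected are already fewer than 4,634 without any misclassification, so the figure does not describe that outcome either.
- *Direction.* A reader might infer that harm must be understated. Tolerance pulls towards no effect. Under-recorded comorbidity among treated joiners would make them look healthier than they are and could inflate apparent harm. The documents do not settle which dominates.
- *Covariates.* Matching takes place at the index date. Even a patient with no earlier record has about 12 months in the antihypertensive and statin cohorts, or three in the antiplatelet cohort, in which diagnoses can be entered. That softens the effect of treating absent records as absent disease, though it does not restore new-user status.
- *Another reading of the exclusion.* If Aim 3 counted only treatment started at or after the index date, and previous meant before the index date, the interval itself would act as a look-back. The exposure window for Aim 3 is not stated. This reading departs from the one given for Aim 1, and the protocol should not leave the choice open.

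None of this supplies the missing minimum. Eligibility is fixed in the protocol, so this is not a detail left to an analysis plan.

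**Conclusion.** The point holds in a limited form. As written, eligibility lets some continuing users enter Aim 3 as new users, mainly in the antihypertensive and statin cohorts, with partial protection for antiplatelets. This rests on exposure being set before the index date in Aim 3 as it is in Aim 1.

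The documents give neither the share affected nor the hazard ratio among such patients. The apparent ratios of 1.095 to 1.07 (or 1.09 to 1.04 if h = 0.9) in place of 1.10 show what assumed shares of 5% to 30% would do through tolerance alone. They are not estimates for this study. With under-recorded history possibly acting in the opposite direction, the size and net sign of the bias are unknown. A large cohort does not reduce it. The change should be made because it is cheap and because the new-user restriction cannot be verified without it.

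**What to change.** For Aim 3 only:

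1. Require at least 12 months of up-to-standard registration before the qualifying reading, risk score or cardiovascular event.
2. State that a previous prescription is any recorded prescription of the exposure class before that date. This keeps the present unlimited exclusion; the 12 months is a minimum period of observation and does not replace it.
3. Define comorbidities from all available history up to the index date. Limiting them to a 12-month window would discard older diagnoses.
4. Repeat the analysis with other look-back lengths as a sensitivity analysis.

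The cost is a few lines of eligibility text and the loss of recently registered patients from Aim 3. The protocol does not give their number; the expected cohort is about 3.3 million. If the age equivalence in Amendment 2 is used to set the statin qualifying date, the protocol should also say how that date is set for people who join above those ages, since the registration rule could otherwise remove all of them.
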